### Arteriovenous fistula

AVF is a communication between an artery and a superficial vein, which is created surgically, and after a maturation period of at least 6 weeks, it allows us to obtain a portion of the superficial vein of good caliber in which the blood flow is sufficiently important to allow the realization of hemodialysis. The AVF must be punctured by a nurse at each session with two large gauge needles to allow sufficient blood flow. This step, which is repeated more than 300 times a year per patient, is crucial to the success of the treatment. The quality of its execution determines the success of the treatment [2]. This procedure requires specific skills [3] to prevent the many complications that can arise from incorrect positioning of the needle in the AVF lumen, pain, hematoma at the puncture site, false aneurysm or pulsatile hematoma, transfixing puncture of the vein, infection, scarring, and even necrosis at the puncture site with a risk of unpredictable AVF rupture and cataclysmic acute bleeding [4].

The psychological aspect must be taken into account, as difficult or even painful punctures often cause apprehension in patients, even real anxiety, and can be a source of deterioration in quality of life.

Finally, the quality of the AVF puncture also impacts the quality of the treatment [5]. In the case of malposition of the needles in the vascular lumen, the blood flow and thus the quantity of blood treated can be greatly reduced. A more severe puncture complication may render the vascular approach unusable for several days [6].

The population of subjects treated in hemodialysis is made up of increasingly older patients with vascular comorbidities and often diabetes. All these factors negatively influence the quality of the vessels for AVF preparation and contribute to increasing the risk of complications related to AVF puncture.

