### Outcomes {12}

The primary outcome is the number of adverse events occurring during AVF puncture in the TT and TTST groups (comparison of percent occurrence of events in each group) defined by any of the following events: unipuncture failure, bipuncture failure, simple hematoma, hematoma not allowing continuation of dialysis.

The secondary outcomes are the number of perdialytic bleeds: accidental needle withdrawal, pain score (numerical scale) experience at the time of puncture, ease or difficulty of puncture, patients’ anxiety score (numerical scale) at the time of puncture, use of ultrasound by the nurse, and type of equipment used for the puncture (needle or catheter).

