
The same number of 4800 punctures for the T5 period (baseline) is also used. This means a total of 9600 punctures over the study period.

Several levels are taken into consideration: center, nurse, patient, and AVF puncture. Within a single center, the overall reflection of activity is related to history, practices, schedules, recommendations, etc. This center-specific activity may differ from one center to another. The experience of the nurses led to the same effects from one center to another, such as the characteristics of the patients and the AVF. These different points are taken into consideration to look for possible differences and effects that could be the cause of confounding factors.

In total, 8 centers participated, with 600 pretraining punctures per center and 600 posttraining punctures per center; that is, 9600 punctures were observed.

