## Statistical methods

### Statistical methods for primary and secondary outcomes {20a}

The difference in percentages between the two groups will be determined by a chi-square test, thus allowing us to meet the main objective. This result will be adjusted according to several criteria, two of them in particular: a center effect, a baseline effect, and an effect of the degree of experience of nurses.

Indeed, the analysis of cluster trials is more complex than the analysis of trials with individual randomization units. The analysis will therefore also be carried out at the cluster level using the guide of the French Health Authority of June 2007 (methodological guide downloadable from www.has-sante.fr).

The secondary objectives (number of per-dialytic bleeds, accidental needle withdrawals) will be analyzed according to the same procedures as for the primary objective. The pain score (numeric scale) at the time of puncture will be analyzed between the two groups by Student’s *t* test.

All the parameters collected will be analyzed.

Multivariate analyses will be considered according to the results of univariate analyses such as logistic regression comparing the two groups and mixed models.

The adjustments described above will also be applied to the secondary objectives.

The collection of the nurses’ feelings of expertise will be synthesized.

All analyses will be based on a first species error of 5% and will be two-tailed.

The IBM®-SPSS® data analysis software (IBM Corp. Released 2015. IBM SPSS Statistics for Windows, Version 23.0. Armonk, NY: IBM Corp.) will support all analyses.

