## Discussion

AVF puncture in patients undergoing chronic hemodialysis is a procedure that nurses repeat many times. The quality of the procedure determines the success of the treatment and the patient’s comfort. This procedure requires specific skills to avoid multiple complications.

Currently, the technique for puncturing AVF is passed by companionship within hemodialysis departments. Standardization of the procedure is part of a drive to optimize practices and continuously improve care. In this study, we expect to observe a significant reduction in pain intensity for patients, as well as a reduction in the number of hematomas. The reduction in these adverse events will lead to an extension of AVF lifespan, an increase in dialysis quality, and possibly a gain in quality of life for the patient.

The strong point of our study is the use of procedural training, which is innovative in several aspects. It is little used in the continuing education of professionals. It enables the team approach to AVF puncture to be conceptualized and then modeled in procedural simulation. The contribution of therapeutic communication in procedural workshops enables a holistic approach to patient management, despite the technical nature of the treatment. Moreover, the evaluation of the direct benefit of training for the patient (Kirkpatrick level 4) is poorly described in the literature.

This study has several limitations. Firstly, data collection concerning the occurrence of adverse events is declarative in nature. Nurses may underreport/overreport the occurrence of events for fear of being judged. This risk is present in both the data collection and the comfort questionnaire. Then, with regard to distance learning, we cannot be totally sure that it is the nurses who log on, carry out the distance learning, and validate the quizzes.

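### The test named for pain is a t test that, read at puncture level, treats repeated scores from the same patients and centers as independent, and no clustered analysis is said to govern pain

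*Protocol article*

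**What the plan says.** The Outcomes section lists, among the secondary outcomes, "pain score (numerical scale) experience at the time of puncture". The section on statistical methods for primary and secondary outcomes assigns it a test: "The pain score (numeric scale) at the time of puncture will be analyzed between the two groups by Student’s *t* test". It does not say whether the observation is a puncture, a patient mean or a center mean. The Sample size section counts punctures throughout: 600 per center and period, 2400 per group.

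Four other statements bear on the point.

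- After the chi-square test for the primary outcome, the result is to be adjusted for "a center effect, a baseline effect, and an effect of the degree of experience of nurses", and later "The adjustments described above will also be applied to the secondary objectives". The patient is not on that list.
- Of the primary analysis the same section says "The analysis will therefore also be carried out at the cluster level". The section on additional analyses repeats this. Neither says whether it covers pain or takes precedence over the t test.
- Mixed models are mentioned only as something to consider once the univariate results are known, with no random effects named.
- The Sample size section acknowledges the structure: "Several levels are taken into consideration: center, nurse, patient, and AVF puncture". It then discusses these levels as sources of confounding, not as sources of correlation.

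On repetition, the background says of fistula puncture: "This step, which is repeated more than 300 times a year per patient, is crucial to the success of the treatment".

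**The concern.** Pain is the patient's own rating. One person's ratings over successive sessions resemble each other more than ratings from different people, and patients treated by one nursing team may also resemble each other. A two-sample t test on punctures counts every rating as new, independent information, so its standard error is too small whenever either correlation is positive.

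At stake is the patient-reported benefit that the Discussion forecasts: "In this study, we expect to observe a significant reduction in pain intensity for patients". If the named test supplies the p-value, a chance imbalance of a few pain-sensitive patients, or one center with a different scoring habit, could be reported as an effect of simulation training.

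**Working it through.** **No figure to reproduce.** The protocol gives no standard deviation, target difference or power for pain. Its count per group does follow: 4 centers × 600 = 2400 punctures per arm per period.

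**Step 1: scores per patient per period.** Inputs: more than 300 punctures per patient per year and two needles per session (Arteriovenous fistula section); 13 to 40 punctures per day by center (Trial design); 600 punctures per center and period (Sample size). This assumes that collection runs consecutively until 600 is reached.

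- Days to reach 600: 600/40 = 15 to 600/13 = 46.
- Counted by needle: 300/365 × 15 = 12 to 300/365 × 46 = 38 scores per patient.
- Counted by session (half of that): about 6 to 19.
- Over the 4 weeks used in the sample size: 300 × 28/365 = 23 by needle, 11.5 by session.

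The 17 to 34 punctures per day given under Recruitment lead to values inside these ranges.

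**Step 2: true error of a puncture-level test, patient correlation only.** The protocol's own inflation formula, applied to the patient as the cluster, gives DE = 1 + (m − 1) × ICC. The true two-sided error of a nominal 5% test is 2 × [1 − Φ(1.96/√DE)]. The within-patient ICC is not in the documents and is assumed over a range.

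| m | ICC | DE | two-sided error | false reduction only (nominal 2.5%) |
|---|---|---|---|---|
| 6 | 0.05 | 1.25 | 8.0% | 4.0% |
| 6 | 0.1 | 1.5 | 11.0% | 5.5% |
| 6 | 0.3 | 2.5 | 21.5% | 10.8% |
| 6 | 0.5 | 3.5 | 29.5% | 14.7% |
| 12 | 0.05 | 1.55 | 11.5% | 5.8% |
| 12 | 0.1 | 2.1 | 17.6% | 8.8% |
| 12 | 0.3 | 4.3 | 34.5% | 17.2% |
| 12 | 0.5 | 6.5 | 44.2% | 22.1% |

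With m = 12 the standard error is too small by a factor √DE of about 1.4 at ICC 0.1 and 2.1 at ICC 0.3. With m = 23 the two-sided error runs from 17.6% (ICC 0.05) to 57.2% (ICC 0.5).

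**Step 3: adding the center.** Simulated two-sided rejection rates with no true effect (4 centers per arm, 600 punctures per center, 12 per patient, 4000 runs per row):

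| patient ICC | center ICC | t test on punctures | t test on patient means | t test on center means (6 df) | paired test on 4 pairs (3 df) |
|---|---|---|---|---|---|
| 0.3 | 0 | 35.7% | 4.8% | 5.3% | 4.9% |
| 0.3 | 0.01 | 53.8% | 19.5% | 4.6% | 5.4% |
| 0.3 | 0.05 | 74.2% | 47.3% | 5.6% | 5.2% |

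The first row agrees with the formula (34.5%). The second shows that averaging within patients is not enough once centers differ even slightly. Only the center-level analyses hold 5% throughout.

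**Step 4: do the listed adjustments help?** The patient is not among them. A fixed center effect cannot repair the comparison in the post-training data alone, because each center lies wholly in one arm and the center terms are then collinear with arm.

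**The case against.** The strongest reply is that the plan is not blind to clustering. It announces a cluster-level analysis, extends its adjustments to the secondary objectives and mentions mixed models. A center-level analysis absorbs repeated scores within patients whatever their correlation, as Step 3 shows. The article also never states the unit of the t test, and the random-effects structure may be left to a fuller document.

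Much of this stands. A reader might infer that pain would be analyzed with no correction at all, and the documents do not support that. What they leave open is which result counts. The cluster-level analysis comes as an addition, in text about the primary outcome. Mixed models depend on the univariate results. The t test is the only method tied to pain by name, and every analysis is declared at 5% two-sided.

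Three further limits are fair. A reader might take the two-sided rates as the chance of a false pain reduction, but that chance is half as large. A reader might also treat a dozen or more scores per patient as given. It is inferred, and by session it may be as few as 6. Finally, pain is a secondary outcome, and the Discussion sentence is an expectation, not a decision rule.

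**Conclusion.** The point holds in a bounded form. The test named for pain, on its natural puncture-level reading, breaks independence at both the patient and the center level, and nothing in the article gives precedence to an analysis that would not. With no center variance, the true two-sided error is about 8-30% with 6 scores per patient and about 12-44% with 12, for ICC 0.05-0.5. For a false reduction alone, halve these and compare with 2.5%. At a center ICC of 0.01 and a patient ICC of 0.3, even a t test on patient means rejects in about 20%.

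These sizes rest on assumed correlations, on scores per patient inferred from stated rates, and on the puncture being the unit. The direction does not depend on the values chosen: any positive correlation raises the error above 5%. It would be tempting to conclude that the patient level is the whole problem and that patient means would solve it. The simulation shows otherwise, because the randomized unit is the center.

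**What to change.** State one inferential analysis for pain, and the same one for anxiety (also a numerical score at puncture), that respects the 8 centers in 4 pairs. Either of these would do:

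- compare center mean scores after training, adjusted for the center's own T5 mean, with inference on the centers or pairs; or
- fit a linear mixed model to the scores with random effects for center and for patient within center, taking account of the pairs and using small-sample inference for the arm effect.

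Say explicitly that this result governs, and keep the puncture-level t test as descriptive only. Use a patient's own T5 mean as a covariate only where the same patient can be linked across periods. The article describes a unique patient number as a feature of the database but also calls data collection anonymous, so linkage should be confirmed first. The center-mean version needs no patient linkage.

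The change is one of wording plus modest analysis work. The cost is wider and less favorable confidence intervals for pain, since inference then rests on 6 degrees of freedom for 8 center means or 3 for 4 pairs, before any baseline adjustment.

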## Objectives {7}

We hypothesize that a training program for nurses on AVF approach in procedural simulation versus theoretical input alone would decrease the adverse events related to AVF punctures and would be beneficial for the patient. As the patient’s management is not modified, only the consequences of the optimization of the procedure will be evaluated through the collection of the number of adverse events occurring during AVF puncture.

The primary objective was to compare the number of adverse events related to AVF puncture between a group receiving theory- and simulation-based training (TTST) and a group receiving only theoretical training (TT).

There were secondary objectives that were to compare the TTST and TT groups: occurrence of other adverse events related to AVF puncture during a hemodialysis session, patients’ experience of pain and anxiety, and nurses’ behavioral changes in medical device use.

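### The logistic and mixed models comparing the arms depend on univariate results, and nothing keeps post-training variables such as ultrasound use out of them

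*Protocol article*

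**What the plan says.** All of the analysis rules are in the protocol article, Statistical methods for primary and secondary outcomes {20a}; the opening part is repeated in Methods for additional analyses {20b}.

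- Main test: "The difference in percentages between the two groups will be determined by a chi-square test, thus allowing us to meet the main objective". An analysis at cluster level is also promised, following a national methodological guide.
- Adjustments named in advance: "This result will be adjusted according to several criteria, two of them in particular: a center effect, a baseline effect", followed by "an effect of the degree of experience of nurses". They extend to the other endpoints: "The adjustments described above will also be applied to the secondary objectives".
- Scope: "All the parameters collected will be analyzed".
- Multivariable models: "Multivariate analyses will be considered according to the results of univariate analyses such as logistic regression comparing the two groups and mixed models".

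Outcomes {12} lists among the secondary outcomes ease or difficulty of puncture and "use of ultrasound by the nurse, and type of equipment used for the puncture (needle or catheter". Objectives {7} includes as a secondary objective the comparison of "nurses’ behavioral changes in medical device use". The Simulation-based training program section makes hands-on ultrasound one of its four modules. The Control arm (TT) section gives the same topic as theory. Who will be blinded {17a} says that blinding is not possible.

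**The concern.** A model that compares randomized arms should be fixed before the outcomes are seen. Here the logistic and mixed models depend on what the univariate analyses show, in a trial without blinding. Two things are at stake.

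1. **Selection.** If a screened model can be run or left out after the univariate results are known, the report can rest on whichever of the two answers is more favorable.
2. **Over-adjustment.** Variables recorded at the post-training puncture can be strongly associated with puncture complications and so pass a univariate screen. Some of them are what the training is meant to change. Conditioning on such a variable takes out the part of the effect that runs through it. The estimate then no longer answers the stated objective, which is the effect of adding simulation to theory.

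**Working it through.** The plan gives no figure on this point, so there is none to reproduce. The check has three parts.

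**1. Which analyses does the conditional rule reach?**
- Chi-square test: no. It is stated without condition.
- Cluster-level analysis: no. It is also stated without condition.
- Adjustment for center, baseline and nurse experience: promised without condition, but no method is named for it. A plain chi-square test of two percentages takes no covariates. The only regression models named in the article are the logistic and mixed models, and those are conditional. The cited guide may supply another method, but the article does not say so.
- Further covariates: no candidate list, no entry rule and no restriction to pre-training variables.

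**2. Size of over-adjustment (assumed values, except the halving).** Sample size {14} plans for 9.3% against 4.65%, a risk ratio of 0.50. Assume that ultrasound is used in 10% of control punctures, that it lowers risk by 40%, and that this effect is the same in both arms and unconfounded.
- Risk multiplier from ultrasound, control: 1 − 0.4 × 0.10 = 0.96.
- Risk multiplier, simulation arm at 50% use: 1 − 0.4 × 0.50 = 0.80.
- Part of the risk ratio that runs through ultrasound: 0.80 / 0.96 = 0.833.
- Risk ratio left after adjustment: 0.50 / 0.833 = 0.60, a 40% reduction in place of 50%.

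Range over the simulation arm's ultrasound use:
- 10% (no change in use): 0.50 / (0.96 / 0.96) = 0.50, so nothing is lost.
- 30%: 0.50 / (0.88 / 0.96) = 0.545, about a 45% reduction.
- 70%: 0.50 / (0.72 / 0.96) = 0.667, about a 33% reduction.

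The same check on the logistic scale: the total odds ratio is (0.0465 / 0.9535) / (0.093 / 0.907) = 0.48. The model is logit p = a + b·arm + ln(OR for ultrasound)·use. Here a and b are solved so that the two arms' overall risks stay at 9.3% and 4.65%, with control use at 10%. The adjusted arm odds ratio is:
- use 30%, ultrasound OR 0.5: 0.53
- use 50%, ultrasound OR 0.5: 0.60
- use 50%, ultrasound OR 0.3: 0.69
- use 70%, ultrasound OR 0.3: 0.88

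**3. Size of the selection effect (illustrative simulation under no effect).** Settings: 8 centers, normally distributed center means, valid center-level tests at two-sided 5%, 2, 4 or 6 candidate covariates screened univariately at p < 0.05 or p < 0.20, baseline correlation 0.3 or 0.6, and 8,000 trials per setting.
- Each single model: close to 5%.
- Either the unadjusted or the screened model significant: 5.5% to 8.6%. A separate rerun gave 5.4% to 8.1%.

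The Monte Carlo standard error near 5% is √(0.05 × 0.95 / 8,000) = 0.24 percentage points, so the low end is barely above nominal.

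**The case against.** A reader might infer that the adjusted result as a whole is picked from the data, or that the primary result is. The text does not support that. Three adjustments are named in advance and repeated in {20b}. The chi-square test is tied to the main objective, and neither it nor the cluster-level analysis passes through the univariate screen.

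A reader might also infer that the trial plans to adjust for ultrasound use or equipment type. It does not say so; it lists them as outcomes. Treating every collected parameter as a candidate covariate joins two separate sentences. That training changes these variables is the trial's expectation, not a fact. The control arm also learns ultrasound in theory, no simulation module is described as covering needle-versus-catheter choice, and Trial design {8} says that all centers use the same device types. The case is therefore stronger for ultrasound than for equipment.

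The direction of the bias is not certain either. If nurses turn to ultrasound for difficult punctures, its association with events is confounded and the adjusted estimate could move differently. The simulation used center means, whereas the sentence concerns logistic and mixed models.

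Two further objections carry less weight. Grammatically, the logistic and mixed models could be examples of the univariate analyses; on that reading the multivariable analyses still depend on univariate results. A candidate list and entry threshold could be left to an analysis plan, but the article does more than leave them out. It states a result-dependent rule, and a plan that fixed the model in advance would have to contradict it.

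**Conclusion.** The point holds in limited form. Beyond the three named adjustments, the multivariable arm comparison is conditional on univariate results, and post-training variables are not kept out. Because no other regression method is named, the route by which the named adjustments would be made is also unclear.

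The size is moderate and rests on assumptions. Adjusting for ultrasound use would turn a true halving into roughly a 33% to 45% reduction if use rises from 10% to between 30% and 70% and ultrasound cuts risk by 40%; nothing is lost if use does not change. The false-positive inflation from a free choice between the unadjusted and the screened model is modest, about 5.5% to 8.6% against 5%. It applies only if either result could support the claim. The analysis text should be corrected, but the point does not undermine the main test.

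**What to change.** Change the wording of {20a}, using data that are already collected:

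- Delete the sentence that makes multivariable analyses depend on univariate results.
- Specify one adjusted model of post-training events that respects the clustering by center and is run whatever the univariate results show. It should contain arm, the named baseline rate and nurse experience. Experience may instead go into a stated sensitivity model: in a center-level regression on 8 centers, intercept, arm and baseline leave 8 − 3 = 5 residual degrees of freedom, and one further covariate leaves 4.
- State that variables measured at or after the post-training puncture (ultrasound use, equipment type, ease of puncture, pain, anxiety) are not adjusters in the arm comparison.
- Label any model built by univariate screening as an exploratory risk-factor analysis.

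The cost is the loss of freedom to adapt the model after seeing the data. No extra data, centers or punctures are needed.
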